## 7. Analysis population

For the purposes of analysis, the following analysis sets are defined:

| Participant Analysis Set     | Description                                                                                            |
|------------------------------|--------------------------------------------------------------------------------------------------------|
| Intention-To-Treat (ITT) Set | All randomized participants who received at least one dose of the intervention treatment. Participants |

|                       |                                                                                                |
|-----------------------|------------------------------------------------------------------------------------------------|
|                       | will be analyzed according to the intervention to which they were allocated.                   |
| Per-protocol (PP) Set | A subset of ITT set without important protocol deviations affecting primary efficacy analysis. |

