## **6.5 Methods of subject assignment**

Participants were randomly assigned (1:1) using blocks of four to receive either MMF (MMF group) or a control treatment (Control group). A statistician from the Clinical Trial Center of Ruijin Hospital, [name], who was masked to trial allocation generated the randomization sequences by a computer algorithm. Then, random numbers were written on the cards and packed in sequentially numbered envelopes that were opened when the patients were enrolled. [name] assigned patients to different groups according to the number on the card. Only Assessors were masked to the group allocation. Eligible subjects were recruited from the Department of Rheumatology and Immunology of Ruijin Hospital and the Department of Rheumatology and Immunology of the other two clinical centers.

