## **7.2 Preparation/handling/storage/responsibility**

### **7.2.1 Responsibility**

The drugs involved in this study were purchased by the patients from the outpatient pharmacy, and each time the dosage was prescribed according to the doctor's prescription.

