### **7.2.4 Preparation**

The intervention drugs are fixed-package tablets and capsules, which require no additional preparation.

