## **8. Statistical procedures**

### **8.1 Randomization and masking**

Participants were randomly assigned (1:1) using blocks of four to receive either MMF (MMF group) or a control treatment (Control group). A statistician from the Clinical Trial Center of Ruijin Hospital, [name], who was masked to trial allocation generated the randomization sequences by a computer algorithm. Then, numbers were written on the cards and packed in sequentially numbered envelopes that were opened when the patients were enrolled. [name] assigned patients to different groups according to the number on the card. Assessors were masked to the group allocation. Eligible subjects were recruited from the Department of Rheumatology and Immunology of Ruijin Hospital and the Department of Rheumatology and Immunology of the other two clinical centers. Doctors were responsible for patient inclusion and regular follow-up assessments ([name], [name], [name], [name], and [name]). The assessment of patient flare was strictly based on the SELENA-SLEDAI Flare Index (including severe flare, and mild to moderate flare) rather than subjective decisions. Data analysts ([name] and [name]) were not involved in patient assessment and treatment, and they were masked to the group allocation.

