### **8.5 Primary outcome**

Flare proportion was defined as categorical variables, data were expressed in the form of frequency (percentages). The primary outcome was the proportion of patients with flares (including mild-to-moderate flares and severe flares) during follow-up. Safety of Estrogens in Lupus Erythematosus National Assessment-Systemic Lupus Erythematosus Disease Activity Index (SELENA-SLEDAI) Flare Index (SFI) was used for assessing disease flares in this trial. Pearson Chi-square or Fisher's exact tests were used to compare between-group differences. We first calculated the total flare rate, and then calculated mild-to-moderate flare rate and severe flare rate, respectively.

For the primary outcome, Bonferroni correction was used and two-sided at a significance level of 0.025. A more stringent statistical criterion was used. Relative risk (RR) was employed to compare the proportion of patients with the end point between MMF group and Control group. Severe flare-free survival proportion was estimated by using the Kaplan-Meier method in the intention to MMF group and Control group with a log rank test. Regarding patients who dropped out of the study, we collected all of the data during follow-up period. For patient who loss to follow-up, we did not collect the data for the subsequent time after lost to follow-up event. We used the ITT set for primary outcome calculation. All of the patients were included in the denominator. We estimated the severe flare-free survival proportion of the MMF group and Control group in both ITT and PP Set using the Kaplan-Meier method.

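### The set called ITT requires at least one dose, and no analysis of all randomised patients is defined, although patients and prescribers know the allocation

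*Combined protocol and SAP*

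**What the plan says.** SAP 7 defines two analysis sets. The one named ITT is "All randomized participants who received at least one dose of the intervention treatment", and its members "will be analyzed according to the intervention to which they were allocated". The per-protocol set is a subset of it without major deviations. There is no third set. The protocol's own statistical section (10) names no analysis set, and SAP 8.6 names none for the secondary outcomes.

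SAP 8.5 states "We used the ITT set for primary outcome calculation" and, in the next sentence, "All of the patients were included in the denominator". It does not say whether that means every randomised patient or every patient in the dosed set.

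Three features of the design bear on this:
- Masking. Protocol 6.5 says "Only Assessors were masked to the group allocation". There is no placebo, and the envelope is opened at enrolment, so patients and prescribers know the arm before the first dose.
- Supply. Protocol 7.2.1 says "The drugs involved in this study were purchased by the patients from the outpatient pharmacy".
- Regimens. Under protocol 7.1.1 both arms take HCQ and prednisone, and only the MMF arm adds MMF.

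**The concern.** An at-least-one-dose rule is usually defended on the ground that not starting cannot depend on the allocated arm. That holds when patients are masked. Here they are not, and one arm has one more drug to buy. Masked assessors and analysts protect how flares are judged and analysed. They do not protect who enters the analysis set.

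If non-starters leave one arm more than the other, and their flare risk differs from that of patients who start, the two groups analysed are no longer the two groups randomised. This would affect the primary result, and because the per-protocol set is nested in the same set, no planned analysis would reveal it.

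**Working it through.** **The plan's own figure.** SAP 6 assumes flare rates of 10% (MMF) and 30% (control). Exact enumeration of the two-sided unpooled Z test with 58 per group gives power 0.8036 and actual alpha 0.0568, as stated. Dropout: 58/(1 − 0.10) = 64.4, rounded up to 65. The sample size reproduces and is not in question.

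**What counts as a dose.** The effect of the rule depends on the undefined term *intervention treatment*.
- Any component of the allocated regimen: a patient who declines MMF but takes HCQ or prednisone stays in. Few would be removed, and the loss need not differ by arm.
- MMF only: no control patient could qualify, so this cannot be meant.
- MMF in one arm and HCQ or prednisone in the other: removal depends on the arm.

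**Illustration under the third reading.** The documents give no number of never-dosed patients, so the number and their flare risk are assumed. Take 65 per arm, control 30%, MMF starters 10%, and k MMF non-starters with flare risk q.

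All-randomised RR = [0.10 × (65 − k) + q × k] / 65 / 0.30. Dosed-set RR = 0.10/0.30 = 0.33.

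| k | q | MMF rate, all randomised | RR, all randomised | RR, dosed set |
|---|---|---|---|---|
| 5 | 50% | (6.0 + 2.5)/65 = 0.131 | 0.44 | 0.33 |
| 5 | 30% | (6.0 + 1.5)/65 = 0.115 | 0.38 | 0.33 |
| 3 | 50% | (6.2 + 1.5)/65 = 0.118 | 0.39 | 0.33 |

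**How much of the gap is bias.** Suppose the control arm holds the same number of comparable patients with the same risk q. For k = 5 and q = 50%, the controls comparable to MMF starters have a rate of (19.5 − 2.5)/60 = 0.283, and the effect in starters is 0.10/0.283 = 0.35. Selection then moves 0.35 to 0.33, and the rest, 0.35 to 0.44, is dilution by patients who took no MMF. For k = 3 the rate is (19.5 − 1.5)/62 = 0.290 and the RR 0.34. For q = 30% there is no selection bias at all.

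**If MMF did nothing.** Assume 30% risk overall in both arms and patients dropped from the MMF arm only. The entries are the false risk difference in percentage points and the rejection rate of the Pearson test at nominal 0.05.

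| Dropped from MMF arm | Their risk 50% | Their risk 70% |
|---|---|---|
| 5% | −1.1; 0.052 | −2.1; 0.058 |
| 10% | −2.2; 0.061 | −4.4; 0.087 |
| 15% | −3.5; 0.073 | −7.1; 0.140 |

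With all randomised patients analysed, rejection is 0.052. If those dropped have average risk (30%), there is no bias.

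**Sensitivity of one result.** Assume control 20/65 and MMF 8/62 after three exclusions: Pearson p = 0.015, below the plan's 0.025. Restoring the three patients with 0, 1 or 3 flares gives p = 0.0105, 0.0205 or 0.064. Only the last changes the conclusion.

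**The case against.** A reader might infer that the rule selectively removes patients who refuse MMF. The documents do not support that. SAP 7 gives both arms an intervention, protocol 7.1.1 describes both full regimens under that heading, and protocol 7.2.4 says "The intervention drugs are fixed-package tablets and capsules". By protocol 7.2.2 the tablets are prednisone and HCQ, and the capsules are MMF. The any-component reading therefore fits the text best, and under it an MMF refuser who takes the background drugs stays in. Nor do the documents report a refusal or a price. Protocol 2.4.1 and 2.4.3 say there is no financial loss, consent precedes enrolment, and unwilling patients are excluded.

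A reader might also infer that SAP 8.5 contradicts SAP 7. The denominator sentence directly follows the one naming the ITT set and can mean everyone in that set, dropouts included. It is ambiguous, not contradictory.

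Nor is the trial wholly unmasked: assessors and data analysts are described as masked, although SAP 8.1 also says "Doctors were responsible for patient inclusion and regular follow-up assessments".

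There are partial safeguards: analysis as allocated, reported numbers of observations (SAP 8.2), a CONSORT diagram (SAP 15), and continued visits after many discontinuations (protocol 8.1). None puts a never-dosed patient back into the primary analysis.

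Finally, widening the set is not enough by itself. If five never-dosed MMF patients leave without flare data and are counted as flare-free, the MMF rate is 6/65 = 9.2% and the RR 0.092/0.30 = 0.31, further from 1 than 0.33. This objection stands, and the fix has to meet it.

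**Conclusion.** The concern holds in a limited form. The primary analysis set is a modified ITT set under the name ITT, its membership rule is undefined by arm, the denominator can be read two ways, and no all-randomised analysis is planned in a trial where patients and prescribers know the allocation. Exclusion for not starting can therefore depend on the arm. It would do so if the dose rule were applied to MMF in one arm and to HCQ or prednisone in the other.

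The direction and size of any bias cannot be derived from the documents. The relative risks of 0.44 and 0.39 against 0.33 rest on assumed numbers and risks of non-starters, and part of each gap is dilution. Bias is small when few patients are excluded or their prognosis is average. It becomes material only when exclusions are both frequent and prognostic. The change is still worth making before analysis, because the set decides the primary result and the correction is mainly wording.

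**What to change.** - Define ITT as all randomised participants, analysed as allocated, whether or not any dose was taken. Use it for the primary and secondary efficacy analyses.
- Rename the present set modified ITT, keep it as supportive, and define *intervention treatment* for each arm.
- State in SAP 8.5 that the primary denominator is all randomised patients.
- Keep following never-dosed patients for flares unless they withdraw consent. Do not count patients without flare data as flare-free by default. State the rule and add a sensitivity analysis.
- Report never-dosed patients by arm.

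The cost is a few lines of SAP text, a little more analysis work, and slight dilution if some patients never start. The planned 65 per arm does not change. On assumed rates (MMF takers 10%, control 30%, never-dosed patients 30% to 40%, all in the MMF arm), exact power of the Pearson test at 0.05 with 65 per arm is 0.83 if everyone starts, 0.78 to 0.75 if 5% of the MMF arm never start, and 0.73 to 0.67 if 10% never start. The dosed-only set would show 0.82 at both 5% and 10%.

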## **8. Statistical procedures**

### **8.1 Randomization and masking**

Participants were randomly assigned (1:1) using blocks of four to receive either MMF (MMF group) or a control treatment (Control group). A statistician from the Clinical Trial Center of Ruijin Hospital, [name], who was masked to trial allocation generated the randomization sequences by a computer algorithm. Then, numbers were written on the cards and packed in sequentially numbered envelopes that were opened when the patients were enrolled. [name] assigned patients to different groups according to the number on the card. Assessors were masked to the group allocation. Eligible subjects were recruited from the Department of Rheumatology and Immunology of Ruijin Hospital and the Department of Rheumatology and Immunology of the other two clinical centers. Doctors were responsible for patient inclusion and regular follow-up assessments ([name], [name], [name], [name], and [name]). The assessment of patient flare was strictly based on the SELENA-SLEDAI Flare Index (including severe flare, and mild to moderate flare) rather than subjective decisions. Data analysts ([name] and [name]) were not involved in patient assessment and treatment, and they were masked to the group allocation.

### **8.2 Analysis principles**

- 1) For the primary outcome assessed at two levels (mild-to-moderate and severe flares), Bonferroni correction was used and two-sided at a significance level of 0.025. Other tests were performed two-sided at the significance level of 0.05. The confidence level for all confidence intervals (CI) will be 95%.
- 2) The number of observations used in the analysis will be reported.
- 3) The statistical analysis plan is drafted prior to database lock, and it includes a detailed description of the statistical analyses. The statistical analyses were performed using SPSS Statistics (version 23.0), GraphPad Prism (version 8.0), and R software

(version 4.0.0). Figures will be plotted using GraphPad Prism (version 8.0) and R software (version 4.0.0).

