### **3. Study outcomes**

#### **3.1 Primary Endpoint:**

The primary outcome was the proportion of patients who have flares (mild to moderate flares and severe flares) defined by modified SELENA-SLEDAI Flare Index (SFI)  at 96 weeks of follow-up.

The definition of mild to moderate flare is the fulfillment of one or more following items:

- 1) variation of SELENA-SLEDAI score  $\geq 3$  (but  $< 12$ );
- 2) new or worsening rashes, cutaneous vasculitis, nasopharyngeal ulcers, serositis, arthritis or fever caused by lupus;
- 3) increase in the dose of prednisone, but less than 0.5mg/kg/day;
- 4) increase of nonsteroidal anti-inflammatory drugs or HCQ;
- 5) Physician's Global Assessment (PGA) (0-3 scale)  $\geq 1$ .

Severe flare is defined as the fulfillment of one or more of the following items:

- 1) change in SELENA-SLEDAI score of more than 12;

- 2) new or worsening central nervous system involvement, vasculitis, nephritis, myositis, thrombocytopenia (platelet  $<60 \times 10^9/L$ ) or haemolytic anaemia (haemoglobin  $<70g/L$  or decrease in haemoglobin level  $>30g/L$ );
- 3) increased usage of prednisone (doubled in dosage or more than 0.5mg/kg/day);
- 4) added cyclophosphamide, azathioprine, methotrexate, mycophenolate mofetil or hospitalization because of lupus activity;
- 5) PGA  $>2.5$ .

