## 4. Study design

In this study, we randomly assigned patients (1:1) to Control group and MMF group. Control group received treatment with HCQ (5mg/kg/day) and prednisone (0.5mg/kg/day); while MMF group received treatment with HCQ (5mg/kg/day) and prednisone (0.5mg/kg/day) plus MMF 500mg twice daily. The dose of MMF stayed the same unless a contrary or severe adverse event occurred.

Prednisone dose was tapered as follows:

Initial dose (0.5mg/kg/day) maintained for four weeks

[figure not shown]

tapered 5mg every two weeks till to 20 mg/day

↓

tapered 5mg every month

↓

gradually to 0.1-0.2mg/kg/day

The taper of prednisone doses was determined by the physicians according to the assessment of patients.

Notes:

- 1) Patients with severe flare were not involved in subsequent treatment plan, but they were still being followed up consistently until the end of the entire process.
- 2) Patients who met the criteria of severe flare were treated with increased doses of prednisone (more than 0.5mg/kg/day), immunosuppressive therapy or hospitalized for treatment according to the patients' condition and the physician's assessment.
- 3) Patients with mild to moderate flares continued to be followed up till the end of Week 96, and all flare episodes were recorded.
- 4) Patients with mild to moderate flares could increase the dose of prednisone (less than 0.5mg/kg/day) or nonsteroidal anti-inflammatory drugs.
- 5) For fever, rash, and arthritis, the dose of prednisone could be used at an initial dose of less than 0.5mg/kg/day, and following the assessment of symptoms, the dose could be increased to more than 0.5mg/kg/day if needed.
- 6) Any sign of kidney involvement (glomerular haematuria and/or cellular casts, proteinuria >0.5g/24hours (or spot urine protein-to-creatinine ratio (UPCR) >500mg/g), unexplained decrease in glomerular filtration rate (GFR)), renal biopsy was suggested to confirm the diagnose of LN. Results of renal biopsy were confirmed by a senior nephrologist ([name]). The treatment of LN was provided according to the European Renal Association-European Dialysis and Transplant Association (ERA-EDTA) guideline.
- 7) The treatment of other organ involvement was provided following the 2019 European League Against Rheumatism (EULAR) recommendation.

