**Table 3 Outcomes of 96-week follow-ups.**

|  | Control group | MMF group | RR | P value |
|--|---------------|-----------|----|----------------|
|  |               |           |    |                |

|                                            | (n=)                  | (n=)                  |          |
|--------------------------------------------|-----------------------|-----------------------|----------|
|                                            | Mean (SD) or
N (%) | Mean (SD) or
N (%) | (95% CI) |
| Primary outcome, %                  |                       |                       |          |
| Proportion of severe flares                |                       |                       |          |
| Proportion of mild to moderate flares      |                       |                       |          |
| Severe flares, %                    |                       |                       |          |
| Lupus nephritis                            |                       |                       |          |
| Neuropsychiatric symptoms                  |                       |                       |          |
| Rash (prednisone dose > 0.5mg/kg/day)      |                       |                       |          |
| Pleurisy                                   |                       |                       |          |
| Thrombocytopenia (<60* 10  /L) |                       |                       |          |
| Pulmonary arterial hypertension            |                       |                       |          |
| Hemolytic anemia                           |                       |                       |          |
| Fever (prednisone dose > 0.5mg/kg/day)     |                       |                       |          |
| Henoch-Schonlein purpura                   |                       |                       |          |
| Moderate mitral insufficiency              |                       |                       |          |
| Arthritis (prednisone dose > 0.5mg/kg/day) |                       |                       |          |

**Mild to moderate flares,  
%**

Arthritis

Rash

Oral ulcer

Fever

Leukopenia  
( $1.5-4 \times 10^9/L$ )

Thrombocytopenia  
( $60-100 \times 10^9/L$ )

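### The two primary tests fall on mild-to-moderate and severe flare rather than on any flare, and the mild-to-moderate proportion can rise when severe flares become milder

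*Combined protocol and SAP*

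**What the plan says.** SAP 3.1 and protocol 9.1 define one primary outcome, which counts patients with a flare of either level. SAP 8.5 repeats it: "The primary outcome was the proportion of patients with flares (including mild-to-moderate flares and severe flares) during follow-up". SAP 6 sizes the trial on one overall flare rate, 10% with MMF and 30% with control.

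The testing rule is attached to the levels. SAP 8.2 states "For the primary outcome assessed at two levels (mild-to-moderate and severe flares), Bonferroni correction was used", with a two-sided level of 0.025, and protocol 10.2 has the same rule. SAP 8.5 gives the order of calculation: "We first calculated the total flare rate, and then calculated mild-to-moderate flare rate and severe flare rate, respectively". It does not say whether the total rate is one of the tests made at 0.025.

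Under its primary-outcome heading, the Table 3 shell has a row for severe flares and a row labelled "Proportion of mild to moderate flares". It has no row for the total.

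SAP 3.1 defines each level as meeting at least one item on a list. No section says how to count a patient who meets items on both lists, or who has a flare of each level at different times.

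**The concern.** No flare, mild-to-moderate flare and severe flare form an ordered outcome. The proportion in the middle falls when mild flares are prevented and rises when severe flares become mild. Both changes benefit the patient, so a test on the middle category alone has no fixed direction of benefit.

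Downgrading is a plausible effect here. The protocol title aims at less main organ involvement, and nephritis, central nervous system disease and myositis are severe-flare items in SAP 3.1. MMF could therefore reduce severity while one of its two primary tests points against it, or shows nothing because the two effects cancel. The plan does not say how a severe-flare result favouring MMF would be read beside a mild-to-moderate result against it. The any-flare comparison, which the outcome definition and the sample size describe, has no stated test among the two.

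**Working it through.** **Inputs.** From SAP 6: 30% control, 10% MMF, 58 per group, 65 after 10% drop-out. From SAP 8.2: two-sided 0.025 per test. From SAP 8.5: Pearson chi-square, all patients in the denominator, so 65 per group is used. Assumed, because the documents do not give them: the split of the control 30% into severe (s) and mild-to-moderate (m), and the fraction f of severe flares that MMF turns into mild-to-moderate ones.

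**1. The plan's own figure.** Exact enumeration of the unpooled Z test at 58 per group, 30% vs 10%, gives power 0.8036, and actual alpha 0.0568 with 30% in both arms. Both match SAP 6. 58 / 0.9 = 64.4, so 65. The sizing is sound for one overall rate at 0.05; no power is given for either level.

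**2. Pure downgrade, each patient counted once at the worst level.** In the MMF arm, severe = s(1 − f), mild-to-moderate = m + sf, and the total stays at s + m = 30%. The mild-to-moderate RR is (m + sf)/m. The probabilities come from exact enumeration of the Pearson test.

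| Control s / m | f | MMF severe / mild | RR, mild | Mild test significant against MMF | Severe test significant for MMF |
|---|---|---|---|---|---|
| 10% / 20% | 0.5 | 5% / 25% | 1.25 | 6.0% | 10.6% |
| 15% / 15% | 0.5 | 7.5% / 22.5% | 1.50 | 12.5% | 18.0% |
| 20% / 10% | 0.5 | 10% / 20% | 2.00 | 25.4% | 25.4% |
| 10% / 20% | 1 | 0% / 30% | 1.50 | 17.8% | 79.1% |
| 15% / 15% | 1 | 0% / 30% | 2.00 | 43.1% | 97.5% |
| 20% / 10% | 1 | 0% / 30% | 3.00 | 75.4% | 99.8% |

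No patient is worse off in any row. For comparison, any flare is 30% vs 30% throughout, with about a 1.3% chance of a significant result against MMF.

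**3. Downgrade plus prevention.** Take 15%/15%, with all severe flares downgraded and half of the original mild ones prevented. MMF mild-to-moderate = 7.5% + 15% = 22.5%, and severe = 0%. Total flares fall from 30% to 22.5%, yet the mild-to-moderate row rises from 15% to 22.5% (RR 1.50).

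**4. Patients allowed to count at both levels.** Let a share q of severe-flare patients also count as mild-to-moderate. Control mild-to-moderate is then m + qs. With 15%/15% and all severe flares downgraded, the MMF rate is 30% and the chance of a significant result against MMF is 43.1% at q = 0, 22.8% at q = 0.25, 10.2% at q = 0.5 and 1.3% at q = 1. The effect disappears only at q = 1, where the mild-to-moderate rate equals the total rate, and SAP 8.5 lists those two separately.

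**5. At the plan's assumed MMF total.** If only 10% of MMF patients flare at all, at most 10% can be mild-to-moderate. The RR is then at most 10/20 = 0.50, 10/15 = 0.67 and 10/10 = 1.0 for the three splits.

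**The case against.** The strongest reply is that any flare is the defined outcome, SAP 8.5 calculates it first, and the severe-flare rate and its Kaplan-Meier analysis move in the right direction. With both levels reported side by side, a shift from severe to mild would be visible. This stands in part. A reader might infer that the plan ignores any flare, and that would be wrong. What is missing is a stated test and a table row for it.

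A second reply is that the reversal is conditional. No section prescribes counting by worst flare, and the lists in SAP 3.1 can overlap: a global assessment above 2.5 also meets the mild-to-moderate threshold of 1. Other items point to separate levels, such as "increase in the dose of prednisone, but less than 0.5mg/kg/day" and the platelet bands in Table 3 (60–100 against below 60). Partial overlap shrinks the effect without removing it. Under the plan's own 10% MMF total it does not arise for the splits examined, so the documents do not support a reading that MMF is likely to look harmful.

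A reader might also argue that the bias persists under any coding because severe-flare patients can no longer record mild flares. SAP 4 note 1 says "Patients with severe flare were not involved in subsequent treatment plan", but goes on to keep them under follow-up, and SAP 8.5 keeps all patients in the denominator. The documents do not establish that stronger claim.

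Finally, two primary tests can disagree under any pairing. That is true, but a middle category adds disagreement caused by benefit itself.

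**Conclusion.** The point holds for the mild-to-moderate test only. SAP 8.2 and protocol 10.2 give half of the primary alpha to a proportion that can rise with benefit, while the comparison that was defined and powered has no stated place in the pair. A reader might infer that the whole primary outcome is reversed; it is not, because the severe-flare test keeps its direction and any flare never rises with a downgrade.

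The size is conditional: a relative risk of 1.25 to 2.0 and about a 6% to 25% chance of a significant result against MMF. This assumes a 30% total in both arms, worst-level counting, half of severe flares downgraded, and control splits of 10/20 to 20/10. It is larger with more downgrading, smaller with overlap or prevention, and absent if every severe-flare patient also counts as mild-to-moderate. The change is worth making because it is cheap and restores agreement with the plan's own definition.

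**What to change.** In SAP 8.2 and 8.5, protocol 10.2 and Table 3, make the two primary tests any flare and severe flare, at 0.025 each. Neither rises when a patient does better; any flare is neutral to a pure downgrade. Add worst flare per patient (none, mild-to-moderate, severe) as a supporting display, which also settles how a patient with both levels is shown, and report mild-to-moderate flare descriptively.

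The same data are used, but one of the two primary tests is replaced, so this is an amendment of substance and should be made before unblinding. It gives up a stand-alone formal claim on mild-to-moderate flare. At 0.025 with 65 per group, any flare at 30% vs 10% has about 75% power (exact Pearson), below the stated 80%; the text should say so.

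Separately, protocol 7.1.1, 7.1.2 and 8.1 and SAP 4 must be reconciled on whether a patient with a severe flare has ended the trial or remains in follow-up.
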